## Abstract

**Introduction:**

Physical activity declines during adolescence, with the lowest levels of activity observed among those with disability. Schools are ideal settings to address this issue; however, few school-based interventions have been specifically designed for older adolescents with disability. Our aim is to investigate the effects of a school-based physical activity programme, involving high-intensity interval training (HIIT), on physical, mental and cognitive health in older adolescents with disability.

**Methods and analysis:**

We will evaluate the Burn 2 Learn adapted (B2La) intervention using a two-arm, parallel group, cluster randomised controlled trial with allocation occurring at the school level (treatment or waitlist control). Secondary schools will be recruited in two cohorts from New South Wales, Australia. We will aim to recruit 300 older adolescents (aged 15–19 years) with disability from 30 secondary schools (10 in cohort 1 and 20 in cohort 2). Schools allocated to the intervention group will deliver two HIIT sessions per week during scheduled specialist support classes. The sessions will include foundational aerobic and muscle strengthening exercises tailored to meet student needs. We will provide teachers with training, resources, and support to facilitate the delivery of the B2La programme. Study outcomes will be assessed at baseline, 6 months (primary endpoint), and 9 months. Our primary outcome is functional capacity assessed using the 6 min walk/push test. Secondary outcomes include physical activity, muscular fitness, body composition, cognitive function, quality of life, physical literacy, and on-task behaviour in the classroom. We will also conduct economic and process evaluations to determine cost-effectiveness, programme acceptability, implementation, adaptability, and sustainability in schools.

**Ethics and dissemination:**

This study has received approval from the University of Newcastle (H-2021–0262) and the New South Wales Department of Education (SERAP: 2021257) human research ethics committees. Findings will be published in peer-reviewed journals, and key stakeholders will be provided with a detailed report following the study.

**Trial registration number:**

Australian New Zealand Clinical Trials Registry Number: ACTRN12621000884808.

Strengths and limitations of this studyOur cluster randomised controlled trial will be adequately powered to detect meaningful changes in the primary outcome functional capacity.Informed by our pilot work, we have tailored the intervention and assessment processes to increase accessibility for the unique study population.The Burn 2 Learn adapted intervention has been designed in consultation with adolescents with disability, and key stakeholders (ie, NSW Department of Education and Special Olympics Australia).Having a unique study population with physical and/or intellectual limitations, not all participants will be able to complete all measures.It might not be possible to blind assessors for all outcomes, as group allocation is often revealed by research participants and teachers during post-test assessments in school-based trials.

## Introduction

Disability is an umbrella term used to describe impairments (ie, problems in body function or structure), activity limitations (ie, difficulty in performing activities), and participation restrictions (ie, difficulty engaging in life situations).^1^ Disability is a worldwide public health and human rights issue with 15% of the global population estimated to be living with disability.^2^ These individuals often face widespread barriers to accessing health and related services, and have poorer health outcomes than those without disability.^3^ As noted in the WHO’s Global Disability Action Plan, the burden of disability can be reduced by addressing the determinants of health, including participation in physical activity.^3^ Individuals with disability are typically less physically active^4^ and more likely to have co-occurring chronic and complex lifestyle diseases^5 6^ than those without disability.

Young people with disability face many common and unique barriers to participation in physical activity. Previous research has identified a range of personal (ie, injury, lack of skills and time to exercise), social (ie, unsupportive peers and parents) and environmental (ie, inadequate accessibility and lack of appropriate programmes), barriers to participation in this population.^7 8^ Conversely, factors shown to facilitate participation include having the time available, being involved in programmes that are adaptable, and exercising in a group with people of a similar age.^9^ Parents also play a critical role in determining whether young people with disability are physically active.^8^ Although parents typically acknowledge the value of physical activity and want their children to be active, many also express concerns about time commitments, balancing the needs of family members, and the suitability of programmes.^8^ To date, the majority of physical activity interventions targeting young people with disability have been conducted in clinical, community, and home settings.^10^

Schools are ideal for physical activity promotion, as they provide access to the adolescent population and have the necessary equipment, facilities, and personnel to deliver programmes.^11^ Physical education (PE) is the primary means of physical activity promotion in schools, and there is a large body of research focusing on the inclusion of children and adolescents with disability in PE classes.^12^ Although teachers typically advocate for inclusion in PE, many lack the confidence and competence to successfully involve students with disability in ways that truly benefit their physical literacy.^12^ Moreover, students with disability often feel marginalised when participating in mainstream PE classes, commonly reporting feelings of social isolation, bullying, and negative social comparisons.^13^ Regardless, simply integrating students with disability into mainstream PE is not enough to produce meaningful changes in health, particularly in the final years of school where there is no mandatory physical activity for students.^14^ In light of this, there is a need for innovative school-based physical activity interventions designed specifically for older adolescents with disability.

Implementing health promotion interventions with older adolescents is challenging, and lack of time is a major barrier to physical activity promotion for this age group.^15^ For older adolescents with disability, the final years of school also involves participation in programmes facilitating transition into postschool pathways (eg, community access and transition to work programmes). Given that adolescents with disability have many competing needs as they prepare for life after schooling, school-based physical activity programmes will have the best chances of adoption if they do not require a substantial time commitment. However, physical activity programmes that provide only a small ‘dose’ of activity are also unlikely to have meaningful health benefits, that is, unless the physical activity offered is of ‘high intensity’.

High-intensity interval training (HIIT) is a time-efficient strategy for improving physical, mental and cognitive health in typically developing adolescents.^16 17^ HIIT sessions generally consist of several short bouts of vigorous activity interspersed with brief periods of light activity or rest. HIIT allows participants to experience similar benefits to other modes of exercise, in less time. Previous studies evaluating school-based HIIT programmes for adolescents with disability have shown improvements in physical health (ie, body composition, aerobic fitness) but have been delivered by physiotherapists or experienced physical educators.^18 19^ Such programmes have limited scalability due to ongoing costs required for intervention implementation. To enhance programme scalability, having classroom teachers implement the intervention has greater potential to change school practice.

We recently conducted a large-scale evaluation of the first teacher-facilitated school-based HIIT intervention, known as Burn 2 Learn (B2L), for older adolescents in mainstream schools.^20–23^ Briefly, teachers were trained to deliver two to three HIIT sessions per week for 16 weeks during students’ regular academic lessons. Positive effects were observed for the primary outcome of cardiorespiratory fitness, as well as a range of secondary outcomes (eg, muscular fitness, mental health, and classroom engagement). Following the success of the intervention, our research team was approached by a local school to adapt the B2L intervention for students with disability. We subsequently conducted a pilot study of the Burn 2 Learn adapted (B2La) programme in one secondary school.^24^ We found it was feasible to train special and inclusive education teachers to deliver the B2La sessions, which were well received by teachers and students. We also found preliminary support for programme efficacy for improving functional capacity and muscular fitness. Following our successful feasibility study, we partnered with the NSW Department of Education and Special Olympics Australia to refine and evaluate B2La in a larger effectiveness trial.

### Study objectives

The primary aim of this trial is to determine the effect of the B2La intervention on functional capacity (primary outcome) in older adolescents with disability. Secondary outcomes include physical activity (accelerometers), muscular fitness, body composition, cognitive function, mental health, physical literacy and on-task classroom behaviour. We will also conduct economic and process evaluations to determine cost-effectiveness, programme efficiency, acceptability, implementation, adaptability, and practicality.

## Methods

### Study design

Our trial is registered with the Australian New Zealand Clinical Trials Registry (ACTRN12621000884808). The reporting of this trial will adhere to the CONSORT^25^ guidelines. The B2La intervention will be evaluated using a two-arm parallel group cluster randomised controlled trial (RCT) with a treatment group and waitlist control group. Assessments will occur at baseline, 6 months (primary endpoint) and 9 months from baseline (secondary endpoint). The RCT will be conducted with two cohorts, one starting in 2022 (10 schools; five intervention and five control) and another starting in 2023 (20 schools; 10 intervention and 10 control). Baseline data collection will occur in the school term preceding intervention delivery (ie, term 1 (February–April 2022 and 2023). The intervention will be delivered during terms 2, 3 and 4 (April–November 2022 and 2023). Immediate postintervention data collection (ie, ~6 months) will occur at the end of term 3 (August–September 2022 and 2023), and follow-up assessments (ie, ~9 months) will be completed in term 4 (November–December 2022 and 2023).

### School recruitment and selection

NSW Government, Catholic and independent secondary schools with student cohorts that include older adolescents (ie, grades 10–12, students aged 15–19 years) with disability will be eligible to participate. Schools will include both mainstream schools with specialist support classes and schools for specific purposes (SSPs). SSPs are dedicated schools for students with moderate-to-high learning and support needs. Eligible schools will be identified, and an expression of interest directed to the school principal. Interested schools will then liaise with the project manager to address any questions or concerns they have prior to returning informed consent.

### Participants

Students at the study schools will be eligible to participate if they are: (1) in Grades 10 to 12 (15–19 years) and identify as living with disability (including neurodevelopmental disability, physical, intellectual or sensory disabilities), (2) able to follow simple verbal instructions in English (as determined by the Index of Social Competence)^26^ and (3) able to participate in vigorous intensity exercise (wheelchair users will be eligible). We will aim to recruit 10 students from each school. We will also recruit two special and inclusive education teachers per school, who will act as school champions and facilitate the delivery of B2La sessions. Special and inclusive education teachers develop and deliver specialised learning programmes for students with a range of disabilities and learning difficulties.

### Sample size and power calculation

Power calculations were based on the primary outcome of functional capacity, assessed using the 6 min walk test (6MWT), which has good reliability in adolescents with disability (intraclass corelation coefficient (ICC)=0.82).^27^ A 6 min push test will be administered for wheelchair users. Although adolescent data are lacking, studies conducted among adult populations with chronic health conditions have reported minimal clinically important differences (MCID) of 24–44 m using the 6MWT.^28^ In our pilot study, we observed a large increase in distance covered from baseline to immediately after the intervention period (163±131 m). However, our pilot study did not include a control group, and effects are typically smaller in effectiveness trials compared with pilot studies.^29^ Based on the pilot data, we estimate a treatment effect of 80 m will represent a MCID in our population. Through simulations (n=10 000) and using data from our pilot study (ie, baseline post-test correlation of *r*=0.60, SD of 90 m and an ICC of 0.2), we have determined we will require a sample of 30 schools with seven participants per school. This sample size will be enough to detect an MCID of 80 m with 90% power at a 5% significance level. Allowing for 30% loss to follow-up at 6 months, we will aim to recruit 10 students from 30 schools (total sample size of 300).

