### Patient and public involvement

Following the B2L cluster RCT, our research team was asked to adapt the intervention for students with disability. We subsequently conducted a feasibility study in one secondary school in Newcastle (n=16 students).^24^ Participating students and teachers were invited to provide feedback on the intervention and suggestions for further improvement. This feedback was then used to refine intervention components (eg, exercise sessions) and develop implementation strategies (eg, professional learning for teachers). We then partnered with the NSW Department of Education and Special Olympics Australia to create B2La. We conducted further testing with teachers and students with disability before progressing to this trial.

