### Statistical analyses

Blinded analyses of the primary and secondary outcomes will be conducted by an independent statistician, using linear mixed models SAS V.9.1 (SAS Institute Inc), with alpha levels set at p<0.05. The models will be used to assess the impact of group (B2La or control), time (treated as categorical with levels baseline, 6 months and 9 months) and the group-by-time interaction. The models will include a random intercept for participant to account for the repeated measures for each participant and a random intercept for school to account for the clustered design. The primary endpoint of the study will be 6 months from baseline. Least square mean differences between the treatment groups will be presented at both follow-up time points, with 95% CIs and p values. Compared with complete case analyses, mixed models include available data for all participants and are thus both more efficient and robust to bias. Mixed model analyses are consistent with the intention-to-treat principle, assuming the data are missing at random. The validity of this assumption will be explored by assessing relationships between missingness and observed values. We will conduct two sensitivity analyses for the primary outcome: (1) multiple imputation (assuming data are missing at random) and (2) complete case analysis (assuming data are missing completely at random). Four potential moderators (ie, socio-economic status, sex, initial weight status and disability type) will be explored using interaction terms (ie, time-by-treatment-by-moderator). If an interaction term is significant (p<0.1), sub group analyses will be conducted.

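### The school ICC of 0.2 is credited to a pilot run in one school, which cannot supply it; the pilot SD also lacks between-school variance

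*Protocol article*

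**What the plan says.** The section on sample size and power describes simulations "using data from our pilot study (ie, baseline post-test correlation of *r*=0.60", and the same bracket goes on to an "SD of 90 m and an ICC of 0.2". As written, all three inputs are pilot data. The section concludes that 30 schools with seven analysed students each will "detect an MCID of 80 m with 90% power at a 5% significance level", and recruits 300 to allow for 30% loss.

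The article describes the pilot twice, with the same reference. The Introduction says: "We subsequently conducted a pilot study of the Burn 2 Learn adapted (B2La) programme in one secondary school". The section on patient and public involvement says: "We subsequently conducted a feasibility study in one secondary school in Newcastle (n=16 students".

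The trial is a "cluster randomised controlled trial with allocation occurring at the school level", and the Statistical analyses section fits "a random intercept for school to account for the clustered design". The ICC that the design needs is therefore the one between schools.

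**The concern.** Between-school variance needs at least two schools. With one, it has zero degrees of freedom, so the pilot cannot be the source of 0.2. This is a wrong statement of source, and not a detail that the full protocol or analysis plan would fill in.

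The same fact affects the SD. An SD observed in one school reflects differences among students of that school only. The trial will take in mainstream support classes and schools for specific purposes (SSPs), across three sectors. Its total SD includes whatever these schools differ by.

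The ICC sets the design effect. A reader who takes 0.2 as observed will place more trust in the stated power than the pilot can support.

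**Working it through.** **Can the ICC come from elsewhere in the article?** The only other ICC in the section, 0.82, is the reliability of the walk test and comes from a cited source. An ICC between classes in the one pilot school would not serve, because schools are randomised. The further testing with teachers and students, mentioned under patient and public involvement, is not described as multi-school data and is not cited for the ICC. No other source for 0.2 is given.

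**Inputs.** From the sample size section: difference 80 m, SD 90 m, r = 0.60, ICC 0.2, 30 schools of seven (15 schools and 105 students per arm), 5% significance. Assumed: two-sided test, equal cluster sizes, the same ICC on every outcome scale, no gain from matching.

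**Formulas.**
- Design effect DE = 1 + (7 − 1) × ICC, which is 2.2, 2.8 and 3.4 at ICC 0.2, 0.3 and 0.4.
- Analysis SD s: post-test only, SD; change score, SD × √(2(1 − r)) = SD × √0.8; ANCOVA, SD × √(1 − r²) = SD × 0.8. For SD 90 m these are 90, 80.5 and 72 m.
- SE = s × √(2 × DE / 105). Power comes from a noncentral t with 28 df (30 schools − 2) and noncentrality 80/SE.

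**The plan's own figure.** At SD 90 m and ICC 0.2, the post-test SE is 90 × √(4.4/105) = 18.4 m and 80/18.4 = 4.34, which gives 98.7% power. The change score gives 99.7% and ANCOVA 99.9%. A simulation of the change score gave 99.6%. None of these is the stated 90%. The dropout step does reproduce: 210/(1 − 0.30) = 300.

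**SD with between-school variance added.** If 90 m is the within-school SD, the total SD at ICC 0.2 is 90/√(1 − 0.2) = 100.6 m.

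**Power for 80 m (%), as post-test / change score / ANCOVA:**

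| Total SD | ICC 0.2 | ICC 0.3 | ICC 0.4 |
|---|---|---|---|
| 90 m | 98.7 / 99.7 / 99.9 | 96.0 / 98.6 / 99.6 | 92.1 / 96.5 / 98.8 |
| 100.6 m | 96.3 / 98.7 / 99.7 | 91.3 / 96.0 / 98.6 | 85.4 / 92.1 / 96.5 |
| 131 m | 82.1 / 89.6 / 94.9 | 72.3 / 81.4 / 89.1 | 63.9 / 73.6 / 82.5 |

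At a total SD of 90 m, power stays at or above 90% up to an ICC of about 0.45 (post-test), 0.60 (change score) or 0.79 (ANCOVA).

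The second row holds the total SD at 100.6 m. If instead the within-school SD is held at 90 m while the ICC rises, the total SD is 90/√0.7 = 107.6 m at ICC 0.3 and 90/√0.6 = 116.2 m at ICC 0.4. Power is then 87.5 / 93.5 / 97.3% and 74.3 / 83.1 / 90.4%.

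**Why 131 m appears.** The pilot change is given as 163±131 m. Using 131 m as the outcome SD on a change score returns 89.6% at ICC 0.2, which is close to the stated 90%. If 131 m is the SD of the change itself, power equals the post-test entries of the last row: 82.1%, 72.3% and 63.9%. An SD of 90 m with r = 0.60 implies a change SD of 80.5 m, which does not agree with that reading.

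**The case against.** The strongest reply is that nothing in the design turns on this. With the stated SD, every analysis assumed keeps power above 92% even at twice the stated ICC, and no document gives an ICC above 0.2. The Blinding and randomisation section also matches schools in pairs before allocation, with school type first and then sector, location and educational advantage. That balances the very differences that could raise the ICC. The value may also have been borrowed from sound data elsewhere.

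Most of this stands, and it limits the consequence. It does not remove the misattribution. Matching balances the arms, but it reduces the variance that the model estimates only if the analysis uses the matching factors. The model as described lists group, time, their interaction and random intercepts for participant and school.

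A reader might infer that the trial is underpowered, because an SD of about 146 m can be solved for at which ANCOVA gives 90%; power at ICC 0.3 and 0.4 is then 81% and 74%. The documents do not support this. They nowhere state such an SD, and it lies outside the 95% interval for an SD of 90 m from 16 students: 90 × √(15/χ²) = 66 to 139 m. That the stated inputs do not return 90% is a separate question about the SD used.

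**Conclusion.** The attribution is wrong as written: an ICC between schools cannot be estimated from a pilot in one school. The pilot SD has the matching gap, worth about 11 m (90 to 101 m) at ICC 0.2 if 90 m is a within-school figure.

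This alone does not show the trial to be underpowered. At the stated ICC, power for 80 m is 98.7–99.9% at SD 90 m and 96.3–99.7% at SD 101 m. At ICC 0.4 it is 92.1–98.8% and 85.4–96.5%. The ICC becomes important as the total SD grows towards 131 m, where the change score gives 90%, 81% and 74% at ICC 0.2, 0.3 and 0.4. The article does not show which SD lies behind its 90%, so a reader cannot tell how much rests on the 0.2.

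These figures rest on the assumptions listed above. The ICC values of 0.3 and 0.4 are an illustrative range and are not taken from the documents.

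**What to change.** 1. In the sample size section, state that ICC 0.2 is an assumption, or give its actual source. State that the SD of 90 m comes from one school and so contains no between-school variance.
2. Restate power over a range of ICC, for example 0.05 to 0.4, with the SD actually used in the simulation. Say whether that is a within-school or a total SD, and reconcile it with the stated 90% and with the 131 m.
3. In the primary model, add school type (mainstream support class or SSP) as a fixed effect. It is the first matching factor, so the analysis would then reflect the matched randomisation, and the mainstream/SSP difference would leave the residual between-school variance.

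Items 1 and 2 cost a few sentences and a small table, with no change in recruitment. Item 3 changes the primary model and should be recorded as an amendment before unblinding. It costs about one school-level degree of freedom (28 to 27). The gain depends on how much of the between-school variance school type explains, which the documents do not say.
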